## **16 Analysis plan and statistical considerations**

### **16.1 Endpoints**

#### **16.1.1 Primary endpoint**

The primary outcome for each audit topic, measured at the patient level and taken from the NCA follow-up audit, is whether a transfusion is categorised as unnecessary or not (binary).

A clinical algorithm for determining if a transfusion is unnecessary or not will be agreed upon by an independent panel of 2 clinicians and a statistician based on clinical relevance and baseline compliance. They will first be presented with a clinical description of candidate endpoints that could be suitable based on the current literature and the basis of the audit. Following this they will then be instructed to discuss the clinical relevance and merits of these endpoints and put forward a list of candidate endpoints they would like to investigate further. For these endpoints we will then present the panel, using a sample of baseline audit, summary information on baseline achievement of the endpoint and the sample size of the final candidate endpoints to make sure that the selected endpoint does not reduce the sample size below acceptable levels or we already have higher compliance than allowed for in sample size calculation. Following a final review of the final candidate endpoints accounting for both the clinical and statistical aspects the panel members will be asked to vote for their preferred outcome with the outcome that has the majority of votes being selected as primary endpoint for the trial. This will minimise the risk of detection bias. The final versions will be included in the Statistical Analysis Plan.

For the surgical audit, transfusion may occur pre-operatively, intra-operatively or post-operatively. There may also be multiple transfusion episodes after surgery but prior to discharge. As all patients will have had one or more transfusions over the entire operative period (14 days prior to surgery to 7 days following surgery), the primary outcome, agreed by the Outcome Review Panel, is whether any of the pre-operative and post-operative transfusions were unnecessary versus all pre-operative and post-operative transfusions being necessary (binary). The statistical algorithm given in the Statistical Analysis Plan will specify the statistical process needed to derive the primary outcome from the patient-level NCA audit. No clinical judgement will be required at a patient-level to categorise transfusions.

For the Haematological audit, there may be multiple transfusions for an individual within the auditing period. In such cases, that patient will be audited once only for one of those events.

A patient may also be transfused with both red cells and platelets in the audit period. In such cases, the patient may provide audit information for both the red cell transfusion and the platelet transfusion. The primary outcome is whether any of these transfusions were unnecessary versus all transfusions being necessary (binary). The statistical algorithm given in the Statistical Analysis Plan will specify the statistical process needed to derive the primary outcome from the patient-level NCA audit. No clinical judgement will be required at a patient-level to categorise transfusions.

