### **5.2.2 Case Identification**

Best practice NCA guidance will be given to Trusts and Health Boards regarding case identification. In addition, this will also allow the trial to minimise the risk of selection bias and allow an assessment of attrition bias. Case Identifiers will generally be Transfusion Practitioners who will work in collaboration with colleagues across the NHS (e.g. informatics) to access hospital lists and databases to identify eligible cases to audit. They will register all consecutive patients meeting eligibility criteria with the NCA. The NCA provide participating Trusts and Health Boards with guidance on how to identify cases. The case identification process will be piloted by the NCA alongside the audit tools.

For the first audit topic, the period of registration will be open to all NHS Trusts / Health Boards for three months. For the second audit topic, the period of registration is one and a half months.

Full details of the case identification used for each audit will be reported in the Statistical Analysis Plan.

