### **6.2 Secondary Objectives of the trials**

Secondary objectives are:

- To generate data to serve as inputs for an investigation of the relative cost-effectiveness of the two feedback interventions compared to usual NCA feedback in each audit topic from a NHS perspective
- To investigate whether the two feedback interventions reduce volume of blood products transfused (i) across specialities within NHS trusts and health boards and (ii) for patients treated in specialities targeted by transfusion topics, when compared to usual feedback, 12 months following randomisation
- To investigate whether two feedback interventions reduce the number of errors (defined in the Statistical Analysis Plan) reported to SHOT, when compared to usual feedback, 12 months following randomisation
- To explore whether there are differential predictors (or moderators) of the effects of the two feedback interventions when compared to usual feedback (i.e. subgroup effects)
- To explore the mechanisms by which the two feedback interventions affect outcome (i.e. mediators of the treatment effect)
- To explore whether the effect of the two enhanced feedback interventions when compared to usual feedback differs according to the transfusion topic

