All eligible cases during the reporting period:

- Consecutive unique patient ID
- Year of birth
- Sex
- Haematological diagnosis
- Transfusion details (Red cell, platelet or both)
- Patient status at time of audit (i.e. audited or notes not available)

All cases that can be audited:

- Weight
- Haematology treatment details
- Participation in clinical trials
- Type of patient (inpatient or day patient)
- Details of Red Cell Transfusion (broad categorisation, clinical indication, pre-transfusion Hb, date, post-transfusion Hb)
- Amount of other red cell transfusions in January
- Details of Platelet Transfusion (broad categorisation, clinical indication, pre-transfusion Hb, date, post-transfusion Hb)
- Amount of other platelet transfusions in January

This dataset will then be sent again for the follow-up audit.

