### **16.1.2 Secondary endpoints**

For the surgical audit *secondary outcomes* are:

1. Total volume of allogeneic RBC transfused (Units at trust-level, from BSMS summed over blood groups and clinical specialities, calculated from net-issue minus wastage)
2. Total volume of allogeneic RBC transfused (Units at patient-level, from NCA summed over pre-operative, intra-operative and post-operative periods);
3. Total number of incidents reported to SHOT (Count at trust-level, from SHOT summed over clinical specialities and events, near misses and “right blood right patient” incidents)
4. Number of definitely, probably or possibly preventable incidents reported to SHOT within clinical specialities targeted by the audit (Count at trust-level, from SHOT summed over events, near misses and “right blood right patient” incidents)

For the Haematology audit *secondary outcomes* are:

1. Total volume of allogeneic RBC transfused (Units at trust-level, from BSMS summed over blood groups and clinical specialities, calculated from net-issue minus wastage)
2. Total volume of allogeneic RBC transfused (Units at patient-level, from NCA)
3. Total volume of platelets transfused (Units at trust-level, from BSMS summed over clinical specialities, calculated from net-issue minus wastage)
4. Total volume of platelets transfused (Units at patient-level, from NCA)
5. Total number of incidents reported to SHOT (Count at trust-level, from SHOT summed over clinical specialities, and events, near misses and “right blood right patients incidents)
6. Number of definitely, probably or possibly preventable incidents reported to SHOT within clinical specialities targeted by the audit (Count at trust-level, from SHOT summed over events, near misses and “right blood right patient” incidents)

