### **18.2 Methods**

Trial-based economic evaluation is not feasible in this instance as no unique set of patients is identified at the start of the trial and followed until study completion. Health economic modelling is therefore required to simulate the costs and outcomes associated with the developed enhancements (separately and combined) as compared with current practice. Two models will be needed, one for patient blood management in surgery and one for haematology as the interventions will target these different transfusion topics and because the costs and adverse event profiles also differ between these components. The models will

be developed jointly by the CI and the project economist following a literature review of previously published models of transfusion, and in accordance with good practice guidelines for decision modelling. A number of transfusion specialists/haematologists external to the project will be asked to comment on the proposed model structure.

The models will combine decision tree and Markov approaches and will be structured so as to simulate the main hypothesised costs and effects. These include the costs associated with delivering standard and enhanced feedback interventions, the potential reduction in unnecessary transfusions and associated adverse events with their costs and consequences, as well as any change in clinical practice occurring to facilitate the reduction in transfusion e.g. for the surgery audit topic this might be better management of pre-surgery anaemia, use of tranexamic acid, or intra-operative cell salvage, all of which have associated costs which must be considered.

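### The patient-level volume outcome counts only transfused patients, so by itself it cannot test whether volume falls among all patients treated in the targeted specialities

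*Protocol*

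**What the plan says.** **Entry to the audit.** For surgery, Protocol section 16.1.1 states "As all patients will have had one or more transfusions over the entire operative period", that period running from 14 days before to 7 days after the operation. For haematology the rule is implied. Among the variables held on every eligible case, section 13.3 lists "Transfusion details (Red cell, platelet or both", with no category for neither. Section 16.1.1 then defines the outcome so that both categories presuppose a transfusion: "The primary outcome is whether any of these transfusions were unnecessary versus all transfusions being necessary (binary".

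**Case finding.** Section 5.2.2 says of the case identifiers: "They will register all consecutive patients meeting eligibility criteria with the NCA". Registration lasts three months for the first topic and one and a half months for the second. Follow-up patients differ from baseline patients (section 7) and are audited about 12 months after randomisation (section 5.2.5).

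**Volume.** Objective (ii) in section 6.2 asks whether volume falls "for patients treated in specialities targeted by transfusion topics, when compared to usual feedback, 12 months following randomisation". The matching surgical outcome in section 16.1.2 is "Units at patient-level, from NCA summed over pre-operative, intra-operative and post-operative periods"; haematology has patient-level NCA volumes of red cells and of platelets. Section 16.3.5 analyses these with a Poisson random-intercept model. The first secondary outcome in each trial is trust-level BSMS volume, summed over clinical specialities.

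**The concern.** The interventions aim to stop transfusions, and the follow-up sample is drawn after they are delivered. Allocation can therefore change who becomes a case. A patient whose every transfusion in the window is avoided does not enter with zero units; that patient is absent.

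The planned safeguards do not reach this. Consecutive registration protects against selection among eligible patients only. Intention-to-treat analysis with imputation (section 16.3.3) fills in unavailable data on cases, not patients who never became cases. The supportive volume analyses by operative stage (section 16.3.5) use the same audited patients. The protocol does not discuss the selection.

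At stake is the reading of objective (ii). Mean units per transfused patient can stay level or rise while the specialities use less blood, and the result would be reported as no reduction or an increase. The primary proportion shares the moving denominator, so its exposure needs checking too.

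**Working it through.** **Inputs.** From section 16.2: 20% unnecessary under usual feedback, with 14% as the target for one intervention. Take 100 patients who would be transfused under usual feedback: U = 20 unnecessary, N = 80 necessary. A fall from 20 to 14 is a 30% cut, a = 0.30. Assumed, because the protocol gives no figures: units per unnecessary case (u) and per necessary case (w), the relative fall in necessary cases (b), and that every avoided patient leaves the audit.

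**Volume, with b = 0.**
- Total before: Uu + Nw. Total after: U(1 − a)u + Nw.
- Units per audited patient: the total divided by 100 before and by 14 + 80 = 94 after.

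| u / w | Total before → after | Change | Units per audited patient | Change |
|---|---|---|---|---|
| 1.5 / 2.5 | 230 → 221 | −3.9% | 2.30 → 2.35 | +2.2% |
| 1 / 2 | 180 → 174 | −3.3% | 1.80 → 1.85 | +2.8% |
| 2 / 2 | 200 → 188 | −6.0% | 2.00 → 2.00 | 0% |

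The change in the total is the change in case numbers times the change in the mean; in the first row, 0.94 × 1.022 = 0.961. The patient-level model sees only the second factor. The mean rises whenever the avoided patients would have received fewer units than average.

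**Primary proportion.** Share = U(1 − a) / [U(1 − a) + N(1 − b)].
- b = 0, all avoided patients leave: 14/94 = 14.9%, against 14.0% on a fixed denominator.
- b = 0, half leave and half stay through another, necessary transfusion: 14/97 = 14.4%.
- b = 10%, 20%, 30%, 40%: 16.3%, 17.9%, 20.0%, 22.6%.

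**Odds ratio, the scale of the planned logistic model.** When all avoided patients leave, OR = (1 − a)/(1 − b). With b = 0 this is (14/80)/(20/80) = 0.70, exactly the 30% cut. On a fixed denominator it would be (14/86)/(20/80) = 0.65. The odds ratio reaches 1 only when b = a and exceeds 1 only when b > a.

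**The case against.** Four points on the other side have weight.

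1. **BSMS volume.** It does not condition on being transfused, stands first among the secondary outcomes, and has gross-issue and transfused-volume versions as supportive outcomes. This stands as a safeguard for objective (i). It is summed over all specialities, so it dilutes a change in the audited one and does not answer objective (ii).
2. **Not every avoided transfusion removes a patient.** A surgical patient spared a post-operative transfusion may still have had an intra-operative one, and a haematology patient may have several transfusions. This stands. The table shows the case where all leave; if fewer leave, the gap between the total and the per-patient change narrows.
3. **The share of audited transfusions that are unnecessary is a legitimate audit target** within a national audit whose processes are to be maintained. This stands for the primary outcome. It does not help objective (ii), which is worded for treated patients.
4. **Detailed case selection is left to the NCA Audit Protocol and the SAP** (section 8.3). For haematology this is a real reservation. For surgery, section 16.1.1 already fixes transfused-only entry.

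A reader might go further and infer that the primary result could be null or reversed despite a real effect. That needs necessary transfusions to fall at an equal or greater relative rate than unnecessary ones. The nearest text is section 18.2, which names "better management of pre-surgery anaemia, use of tranexamic acid, or intra-operative cell salvage" as things that might change for the surgical topic. It gives no size, and it names nothing comparable for haematology.

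**Conclusion.** The point holds for the patient-level volume outcome and should be fixed. It is explicit for surgery and inferred for haematology. Under the assumed units, a 30% cut in unnecessary cases lowers total units by 3.3% to 6% while units per audited patient change by 0% to +2.8%. These sizes rest on the assumed units and on all avoided patients leaving. That the outcome is conditional on transfusion does not rest on either assumption.

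For the primary outcome the effect is modest: 14.0% becomes at most 14.9% if only unnecessary transfusions fall, and when all avoided patients leave the odds ratio equals the relative cut in unnecessary cases. The documents do not support calling the primary result likely to be missed or reversed.

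Nor do they support calling the trial underpowered on this ground. Section 16.2 sets its percentages for unnecessary transfusions at follow-up on auditable cases, which is the audited proportion itself.

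**What to change.** **Wording.** State in sections 16.1 and 16.3.5 that the primary and patient-level volume results apply to transfused patients, and that units per audited patient will not be read alone as the test of objective (ii).

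**Supplementary trust-level count models by arm**, each adjusted for the trust's own baseline-audit count:
- both trials: registered (transfused) cases per fixed registration period;
- both trials: patients with an unnecessary transfusion, scaled by registered over audited cases where notes were unavailable;
- surgery: total audited units, scaled in the same way.

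For haematology, section 13.3 records the audited transfusion and the amount of other transfusions in January only. Any unit total must be limited to the period those data cover; it cannot be built over the one and a half months of registration.

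**Cost.** Protocol and SAP wording and a few cluster-level models. Section 13.3 already provides for data on all eligible cases, including audit status, at baseline and follow-up.

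**Downside.** Trust counts are noisier than patient-level means and depend on complete registration. Registration is generally done by Transfusion Practitioners, who belong to the teams receiving the interventions, so allocation could affect it. Report registration and audit completeness by arm and treat these analyses as supportive. If the NCA Audit Protocol caps the number of cases a site registers, the registered-case count would not be interpretable; this should be confirmed first.

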### **16.1.2 Secondary endpoints**

For the surgical audit *secondary outcomes* are:

1. Total volume of allogeneic RBC transfused (Units at trust-level, from BSMS summed over blood groups and clinical specialities, calculated from net-issue minus wastage)
2. Total volume of allogeneic RBC transfused (Units at patient-level, from NCA summed over pre-operative, intra-operative and post-operative periods);
3. Total number of incidents reported to SHOT (Count at trust-level, from SHOT summed over clinical specialities and events, near misses and “right blood right patient” incidents)
4. Number of definitely, probably or possibly preventable incidents reported to SHOT within clinical specialities targeted by the audit (Count at trust-level, from SHOT summed over events, near misses and “right blood right patient” incidents)

For the Haematology audit *secondary outcomes* are:

1. Total volume of allogeneic RBC transfused (Units at trust-level, from BSMS summed over blood groups and clinical specialities, calculated from net-issue minus wastage)
2. Total volume of allogeneic RBC transfused (Units at patient-level, from NCA)
3. Total volume of platelets transfused (Units at trust-level, from BSMS summed over clinical specialities, calculated from net-issue minus wastage)
4. Total volume of platelets transfused (Units at patient-level, from NCA)
5. Total number of incidents reported to SHOT (Count at trust-level, from SHOT summed over clinical specialities, and events, near misses and “right blood right patients incidents)
6. Number of definitely, probably or possibly preventable incidents reported to SHOT within clinical specialities targeted by the audit (Count at trust-level, from SHOT summed over events, near misses and “right blood right patient” incidents)

### **16.1.3 Tertiary endpoints**

For the surgical audit, *supportive outcomes* are:

1. Pre-operative transfusion (Unnecessary/Grey/Necessary, from NCA)
2. Intra-operative transfusion (Unnecessary/Grey /Necessary, from NCA)
3. Post-operative transfusion (Unnecessary/Grey /Necessary, from NCA)
4. Individual NCA audit standard met (Yes/No, from NCA)
5. Proportion of NCA audit standards met (from NCA)
6. Total volume of RBC issued (Units at trust-level, from BSMS gross issue data)
7. Total volume of RBC transfused (Units at trust-level, from BSMS transfused data)
8. Pre-operative volume of allogeneic RBC transfused (Units at patient-level, from NCA)
9. Intra-operative volume of allogeneic RBC transfused (Units at patient-level, from NCA)
10. Post-operative volume of allogeneic RBC transfused (Units at patient-level, from NCA)

For the Haematology audit, *supportive outcomes* are:

1. Red blood cell transfusion alone (Unnecessary/Grey/Necessary, from NCA)
2. Platelet transfusion alone (Unnecessary/Grey/Necessary, from NCA)
3. Individual NCA audit standard met (Yes/No, from NCA)
4. Proportion of NCA standards met (from NCA)
5. Total volume of RBC issued (Units at trust-level, from BSMS gross issue data)
6. Total volume of RBC transfused (Units at trust-level, from BSMS transfused data)
7. Total volume of Platelets issued (Units at trust-level, from BSMS gross issue data)
8. Total volume of Platelets transfused (Units at trust-level, from BSMS transfused data)

For the surgical audit, patient-level *process variables* include:

1. Whether the planned surgery date equals the actual surgery date;
2. Volume of post-operative cell salvage transfused;
3. Hb level;
4. Length of post-operative hospital stay.

For the haematology audit, patient-level *process variables* include:

1. Whether the platelets transfused were HLA matched or not;
2. Hb level;
3. Platelet count.

For both the surgical and haematological audit, trust-level process data will be collected on:

1. Intervention Fidelity
2. Organisational structures and resources
3. Tier of Data Collectors

## 16.2 Sample size

The sample size calculation has been refined following the grant application in light of decisions regarding the feedback interventions and transfusion topics. For each topic, there are two principal comparisons of interest (1. enhanced feedback documents vs. usual documents; and 2. Post-feedback support vs. no post-feedback support), relating to the two main effects of the 2X2 factorial design. Assuming that there will be 20% unnecessary transfusions at follow-up for each topic, that the ICC will be 0.05 and that cluster sizes will vary from 17 to 68 with a mean of 45, we need 152 clusters to detect a minimally important reduction of 6% (i.e. to 14% unnecessary transfusions) in the presence of, at most, a small antagonistic statistical interaction (i.e. 10% or fewer unnecessary transfusions in the enhanced feedback documents and post-feedback support) with 80% power using logistic regression models, with a random-intercept for cluster, and a 2-sided 2.5% significance level, for each comparison within each model. This requires us to recruit from England, Wales, Scotland and Northern Ireland and allows 12/171 (7%) clusters to be ineligible and 95% of those eligible to consent and be randomised. If these assumptions do not all hold, the tables below illustrate the impact on the minimally important clinical difference the trial would be powered to detect.

**Table 2: Sensitivity Analyses for ICC and recruitment assumptions fixing the power to detect the main effects at 80% & baseline proportion of unnecessary transfusions at 20%**

| ICC         | 150 Clusters   | 140 Clusters    | 130 Clusters    |
|-------------|----------------|-----------------|-----------------|
| 0.05 | (20, 14, 10.0) | (20, 13.5, 9.8) | (20, 13.0, 9.5) |
| 0.06 | (20, 13, 9.5)  | (20, 12.5, 9.3) | (20, 12.5, 8.9) |

|             |               |                 |                 |
|-------------|---------------|-----------------|-----------------|
| 0.07 | (20, 13, 9.0) | (20, 12.0, 8.8) | (20, 12.0, 8.4) |
| 0.08 | (20, 12, 8.5) | (20, 11.5, 8.3) | (20, 11.5, 7.9) |
| 0.09 | (20, 12, 8.0) | (20, 11.0, 7.8) | (20, 11.0, 7.4) |
| 0.10 | (20, 11, 7.8) | (20, 10.5, 7.5) | (20, 10.5, 7.0) |

**Note:** The first number in brackets (i.e. 20) is the proportion of unnecessary transfusions in the standard/standard arm. The second number is the largest proportion of unnecessary transfusions we could detect with 80% power in either the enhanced/standard or standard/enhanced arms. The last number is the largest proportion of unnecessary transfusions we could have in the enhanced/enhanced arm to be able to detect the main effects with 80% power. The power to detect the interaction ranges from 5% to 25% under these scenarios.

**Table 3: Sensitivity Analyses for ICC and recruitment assumptions fixing the power to detect the main effects at 80% & increasing the baseline proportion of unnecessary transfusions to 30% or 40%**

| ICC         | 150 Clusters     | 140 Clusters     | 130 Clusters     |
|-------------|------------------|------------------|------------------|
| 0.05 | (30, 23.0, 18.1) | (30, 22.5, 17.7) | (30, 22.0, 17.3) |
| 0.06 | (30, 22.5, 17.3) | (30, 22.0, 17.0) | (30, 21.5, 16.5) |
| 0.07 | (30, 22.0, 16.7) | (30, 21.5, 16.2) | (30, 21.0, 15.8) |
| 0.08 | (30, 21.5, 16.0) | (30, 21.0, 15.6) | (30, 20.5, 15.1) |
| 0.09 | (30, 21.0, 15.4) | (30, 20.5, 15.0) | (30, 20.0, 14.5) |
| 0.10 | (30, 20.5, 14.9) | (30, 20.0, 14.4) | (30, 19.5, 13.9) |
| ICC         | 150 Clusters     | 140 Clusters     | 130 Clusters     |
| 0.05 | (40, 32.0, 26.9) | (40, 31.5, 26.4) | (40, 31.0, 26.0) |
| 0.06 | (40, 31.5, 26.0) | (40, 31.0, 25.5) | (40, 30.5, 25.1) |
| 0.07 | (40, 31.0, 25.2) | (40, 30.5, 24.7) | (40, 30.0, 24.2) |
| 0.08 | (40, 30.5, 24.5) | (40, 30.0, 24.0) | (40, 29.5, 23.4) |
| 0.09 | (40, 30.0, 23.8) | (40, 29.5, 23.2) | (40, 29.0, 22.7) |
| 0.10 | (40, 29.5, 23.0) | (40, 29.0, 22.5) | (40, 28.5, 22.0) |

**Note:** The first number in brackets is the proportion of unnecessary transfusions in the standard/standard arm. The second number is the largest proportion of unnecessary transfusions we could detect with 80% power in either the enhanced/standard or standard/enhanced arms. The last number is the largest proportion of unnecessary transfusions we could have in the enhanced/enhanced arm to be able to detect the main effects with 80% power. The power to detect the interaction ranges from 4% to 9% under these scenarios.

The worst case scenario is highlighted in grey. Under this, the minimum sample size would be required, that is 5940 patients to provide outcome data (i.e. 1485 patients across 132 clusters). The target sample size is 6840 patients to provide outcome data (i.e. 1710 patients and 38 clusters in each of four arms). The assumptions underlying the sample size calculation will be monitored throughout the project and any deviations reported to the oversight committees.

